## Abstract

**Background:**

Major depressive disorder (MDD) is a significant contributor to the global burden of disease, with a high prevalence in Pakistan. MDD is treatable, and eye movement desensitization and reprocessing (EMDR) therapy is recognized as an effective treatment worldwide. However, EMDR therapy, rooted in Western psychological frameworks, may require cultural and methodological adaptation to fit clients’ needs in Pakistan. Notably, there is a lack of research on adapting EMDR therapy in Pakistan, and scarce studies on its effectiveness through online modalities. To bridge these research gaps, this study has two aims: first to develop an adapted DeprEnd EMDR therapy protocol in Pakistan; second, to test its feasibility, relevance, and clinical effectiveness across in-person and online modalities.

**Methods:**

This research adopts a mixed-mode exploratory sequential randomized controlled trial design. In the first phase, an exploratory qualitative approach will be utilized to culturally and methodologically adapt DeprEnd EMDR therapy protocol through narrative review and focus group discussion. Data will be qualitatively analyzed. This phase has been previously reported in a separate peer-reviewed publication. In the second phase, a randomized controlled trial design will be used to test the feasibility, relevance, and clinical effectiveness of the adapted DeprEnd EMDR therapy protocol. Initially, it will be pilot tested among 25 handful clients, and later an estimated sample of 80 clients will be selected to test it on a large scale. Clients will be randomized via a covariate-adaptive technique to in-person and online arms with a 1:1 ratio. Symptom-related data will be collected at the baseline, midpoint, post-treatment, and follow-up stages. Data will be analyzed using a combination of univariate and multivariate statistics.

**Discussion:**

This research conducts the first known scientific adaptation and clinical testing of the DeprEnd EMDR therapy protocol in Pakistan. Through systematic adaptation and assessment of its feasibility and clinical effectiveness, this protocol is positioned to be scalable, showing potential for broader dissemination across South Asia. It contributes a vital framework for culturally sensitive mental health interventions that bridge global evidence-based practices and local sociocultural needs. This study paves the way for collaborative efforts to optimize trauma-focused psychotherapies in low-resource contexts, thus promoting health equity in the region.

**Trial registration:**

The initial study protocol was registered in the ClinicalTrials.gov database under registration no: NCT-06439043. Last Updated:01/21/2025 and Initial Release:05/27/2024.

**Supplementary Information:**

The online version contains supplementary material available at 10.1186/s13063-026-09543-4.

## Administrative information

Note: the numbers in curly brackets in this protocol refer to SPIRIT checklist item numbers. The order of the items has been modified to group similar items (see http://www.equator-network.org/reporting-guidelines/spirit-2013-statement-defining-standard-protocol-items-for-clinical-trials/).

## Introduction

### Background and rationale {6a}

#### The state of mental health in Pakistan

In Pakistan, mental health is shaped by socioeconomic, cultural, infrastructural, and political conditions, leading to high rates of untreated mental health conditions—such as depression and anxiety—particularly among marginalized groups [1]. Recent statistics show that around 24 million people in Pakistan need mental health care [2]. Moreover, literature reports a high prevalence of depressive disorders in Pakistan. A recent study published in the Lancet reported a 79% prevalence of depression in Pakistan [3]. Similarly, a meta-analysis of 7652 university students across 26 studies published in Pakistan identified a pooled depressive symptom prevalence of 42.70% (95% CI: 34.8–50.9%) [4]. Furthermore, studies by Khan et al. [4], Khattak et al. [5], Ullah et al. [6] and Sana [7] have reported a significant prevalence of depressive symptoms in Pakistan. However, limited professional health resources in the country impact treatment accessibility and quality of care for individuals seeking mental health services. This issue is exacerbated by a lack of mental health awareness and stigma surrounding mental illness in the country [8]. These prevalence findings clarify the local epidemiology of depression in Pakistan and highlight a critical gap: the need for local research to culturally adapt evidence-based treatments. Addressing this gap is vital for improving domestic mental healthcare and contributing effective models to global psychiatry.

#### Treatment of major depressive disorder

Major depressive disorder (MDD) is treatable either through psychotherapy or pharmacotherapy. However, findings of recent systematic reviews revealed that psychotherapy is more efficacious, particularly in the long-term treatment of MDD [8–10]. Furthermore, research indicates that pharmacotherapy is associated with side effects [11] and withdrawal symptoms [12]. Given these risks, pharmacotherapy should be prescribed judiciously. Psychotherapy may serve as a beneficial first line or adjunctive treatment for depression.

Among the most recognized evidence-based psychotherapies are eye movement desensitization and reprocessing (EMDR) [13] and cognitive behavioral therapy [14]. CBT is a well-established approach with decades of research supporting its efficacy. EMDR therapy, though developed more recently, has gained substantial empirical support, particularly for trauma. EMDR therapy is an eight-phase psychotherapy that is based on Adaptive Information Processing theory that targets maladaptively stored memories, and via its bilateral stimulation technique, it reprocesses such memories to a more adaptive state [15]. However, as a newer modality, EMDR requires further investigation to clarify its full range of applications. In Pakistan, CBT was introduced in the early 1990s. Since then, CBT has been widely acknowledged for diverse mental health disorders across the country [16]. However, CBT still faces limitations including issues related to accessibility in rural clinical settings, cultural mismatches, and systemic issues like lack of research funding [17]. In contrast, EMDR therapy remains a relatively emerging intervention in Pakistan. It was first introduced in Pakistan via the EMDR Europe Humanitarian Assistance Programs Project after the 2005 earthquake [18]. EMDR therapy has undergone limited localized adaptation and lacks sufficient region-specific research to validate its efficacy and cultural appropriateness in Pakistan [19].

More specifically, the recently introduced DeprEnd EMDR therapy protocol for depression [17, 18] has primarily been tested in developed countries, such as Germany [20]. The DeprEnd EMDR differs from the standard EMDR therapy protocol since it systematically targets depressive core memory networks rather than focusing primarily on discrete traumatic events [21]. However, to our knowledge, no published studies have clinically tested the DeprEnd EMDR therapy protocol in Pakistan. This significant research gap highlights the urgent need for rigorous scientific research in the Pakistani context. Addressing this gap would not only advance local trauma care but also enrich the global EMDR evidence base through diversification.

#### The necessity of adapting and testing EMDR therapy in Pakistan

EMDR therapy was developed in the USA and is grounded in Western psychological frameworks [22]. Its clinical efficacy has primarily been established in Western countries such as the UK [23], the USA [24], and Australia and New Zealand [25], and other counties including Turkey [25], Japan [26], and China [27]. In Pakistan, relatively few studies have assessed the efficacy of EMDR therapy. Early work by Ali and Rana [28] documented clinically meaningful reductions in post-traumatic stress symptoms among survivors of the 2005 earthquake using EMDR. Subsequent case-based investigations by Bilal et al. [29] and Muhammad Sami et al. [30] reported symptom improvement in patients with complex post-traumatic stress presentations, suggesting the potential utility of EMDR beyond standard PTSD cases, albeit within small and methodologically limited samples. More recently, Khan, Madihie et al. [31] conducted a full-scale randomized controlled trial comparing EMDR with cognitive behavioral therapy for PTSD in Pakistan, demonstrating comparable or superior clinical outcomes for EMDR and providing the strongest empirical support to date for its effectiveness in the local context. Despite these contributions, the existing literature on EMDR therapy in Pakistan remains limited in scope, with most studies focusing on trauma-related disorders, relying on small samples or case-based designs, and lacking systematic cultural adaptation, implementation, and modality-comparison research. Moreover, past research predominantly focused on in-person delivery, leaving online modalities critically underexplored.

The existing literature is also significantly limited to cultural and methodological adaptations in EMDR therapy. Literature reports studies conducted in Cambodia [32] and Iran [33]; additionally, in Syria [34] and Germany [35], and finally, in five African countries [36]. While in Pakistan, studies are very scarce. Farrell et al. [37] recommended that Pakistani therapists must be culturally sensitive, and future research should be carried out on the cultural adaptation of EMDR therapy. In this regard, a recent study by Khan et al. [19] adapted EMDR therapy for post-traumatic stress disorder in Pakistan. Methodological adaptations of EMDR in similar contexts have also been limited, focusing primarily on modifications to the history taking, preparation, and assessment phases [31, 37–40].

The scarcity of research on adapting and clinically testing EMDR therapy in Pakistan, particularly in relation to online delivery formats and recently introduced the DeprEnd EMDR therapy protocol, is largely attributable to the relatively recent introduction of EMDR therapy in the country and the limited availability of trained clinicians. This gap is not merely methodological but reflects a broader neglect of implementation considerations that are central to mental health service delivery in Pakistan. In Pakistan, where mental health services are concentrated in urban centers and specialist availability is limited, reliance on exclusively in-person psychotherapy substantially restricts treatment reach [41]. Consequently, the limited exploration of online EMDR therapy is particularly consequential. However, online psychotherapy offers a viable pathway to reduce geographic, logistical, and financial barriers, and to extend specialist care to underserved populations. Evaluating online delivery is thus not a peripheral technical issue but a core implementation question, especially for interventions intended to be scalable and sustainable in real-world clinical systems. Within this context, the DeprEnd EMDR therapy protocol represents a particularly important case, as it remains insufficiently studied in terms of cultural adaptation and clinical validation in Pakistan. The cultural and methodological adaptation of the DeprEnd protocol has been reported in detail in a separate peer-reviewed publication [42]. Accordingly, the present manuscript focuses on the subsequent pilot feasibility assessment and randomized controlled evaluation of the adapted intervention, with a concise summary of the adaptation process provided solely to maintain conceptual continuity.

#### Theoretical basis of study

Figure 1 presents relevant theories in a grid format, mapping their relevance to the constructs of this study. In the top-left quadrant, the first three theories address the clinical mechanism of EMDR therapy and depression-anxiety reciprocal links. To the right are theories on the cultural adaptation of EMDR therapy. The bottom row contains theories on methodological adaptation (left) and theories on feasibility, acceptance, and clinical effectiveness (right).

**Fig. 1 Fig1:**
[figure not shown]
A conceptual grid of theories informing this study

### Objectives {7}

Against this background and the aforementioned research gaps, the present study has the following three objectives:To develop an adapted DeprEnd EMDR therapy protocol that is culturally and methodologically appropriate for the treatment of major depressive disorder in Pakistan.To assess feasibility and acceptance of the adapted EMDR therapy for its delivery through in-person and online modes in Pakistan.To assess the clinical effectiveness of the adapted DeprEnd EMDR therapy protocol across in-person and online settings.

Table 1 further provides the alignment of research objectives with the theoretical background of the study. The first objective of this study is grounded in theories such as Cultural Sensitivity Theory and the Adaptive Treatment Framework. These theories provide the conceptual basis for two premises: (a) therapies should be adapted both culturally and methodologically to meet the needs of clients and therapists, and (b) guidelines are required to identify the specific cultural and methodological elements to be included in adapted EMDR therapy. The second objective is guided by theories of Technology Acceptance and Therapy Implementation Outcomes. These models emphasize that user acceptance is a critical factor in determining the successful implementation of therapy. Moreover, understanding how users perceive and accept a therapy determines its feasibility. Finally, the third objective is theoretically anchored in the Adaptive Information Processing model, which explains symptom reduction through memory reconsolidation, while the Tripartite Model provides a complementary framework for examining depressive-anxiety symptomatology.

**Table 1 Tab1:** Aligning study objectives and theoretical background

Research objectives	Theoretical basis
To develop an adapted DeprEnd EMDR Therapy protocol that is culturally and methodologically appropriate for treatment of Major depressive disorder in Pakistan	i. Cultural Sensitivity Theory [43] ii. Cultural Competence Theory [44] iii. Adaptive Treatment Framework [45] iv. Behavioral Intervention Model [46]
To assess feasibility, and acceptance of the adapted EMDR therapy for its delivery through in-person and online modes in Pakistan	i. Technology Acceptance Model [47] ii. Therapy Implementation Outcomes Model [48] iii. Medical Research Council Model [49]
To assess the clinical effectiveness of the adapted DeprEnd EMDR therapy protocol across in-person and online settings	i. Adaptive Information Processing Theory [50] ii. Predictive Processing Model of EMDR [51] iii. Tripartite Theory [52]

Taken together, the theoretical models outlined above formed an integrated explanatory foundation for the objectives of this study. Cultural Sensitivity and Adaptive Treatment frameworks justify the need for modifying the DeprEnd EMDR protocol to fit the Pakistani sociocultural and clinical context. Technology Acceptance and implementation models explained the conditions under which the adapted intervention can be practically and acceptably delivered across in-person and online modalities. Finally, the Adaptive Information Processing and Tripartite models provide a mechanistic rationale for expected symptom change in depression and its comorbid anxiety. This theoretical integration ensures that each research objective and corresponding hypothesis is conceptually grounded rather than merely empirically motivated.

## Hypotheses of study

Since the second phase of this study deals with clinical effectiveness, the following directional hypotheses will be tested:i.The adapted EMDR therapy will demonstrate a high level of feasibility, usability, acceptance, technical operability, and safety when delivered through in-person and online modes.ii.The online delivery of the adapted EMDR therapy is non-inferior to the in-person mode for treating major depressive disorder in Pakistaniii.The adapted EMDR therapy will bring about significant temporal reduction in the major depressive disorder symptoms across in-person and online modes.iv.The major depressive disorder symptoms are reciprocally linked to the comorbid generalized anxiety disorder symptoms in a manner that treatment conditions moderate this relationship.

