## Interventions

### Explanation for the choice of comparators {6b}

The comparator is the in-person delivered EMDR therapy and is selected as the active control because it represents the current evidence-based standard of care for the treatment of depressive disorder [66]. Online EMDR therapy is an experimental intervention under investigation for non-inferiority. This design allows determining whether the novel online delivery method preserves therapeutic efficacy while offering potential accessibility benefits.

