### Intervention description {11a}

This trial employs the evidence-based DeprEnd EMDR therapy protocol for depressive disorders [67]. This protocol is specifically optimized for depressive disorders through modifications in:History-taking (focused on depressive triggers vs. trauma),Preparation (enhanced psychoeducation on depression maintenance), andInstallation (targeting depressive cognition reprocessing) [21].

The DeprEnd EMDR therapy protocol has been culturally and methodologically adapted for the Pakistani context, and the full adaptation process has been published elsewhere [42]. In the present trial, both study arms follow the same adapted protocol, differing only in mode of delivery. The intervention will be delivered over 10–14 weekly sessions, depending on individual clinical presentation and treatment response. Each session will last approximately 60–90 min, consistent with standard EMDR therapy practice.In-person EMDR therapy will be delivered by EMDR-certified therapists in selected psychotherapy clinics. Sessions will follow the adapted DeprEnd EMDR protocol using standard face-to-face procedures, including therapist-guided bilateral stimulation and adherence to protocol fidelity requirements.Online EMDR therapy will be delivered via the BilateralBase platform, a validated telehealth system developed in the UK [68]. Therapists and clients will connect synchronously via secure video conferencing using a computer or mobile device. The platform provides visual and auditory bilateral stimulation, real-time therapist guidance, and session structuring consistent with in-person EMDR delivery. Session recordings are enabled for fidelity monitoring, with appropriate consent and ethical safeguards. Apart from delivery modality, the content, session structure, and therapeutic procedures remain equivalent to those used in the in-person arm.

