Furthermore, following the procedures outlined by George and Mallery [84], General Linear Model Repeated Measures (GLM-RM) analyses will be conducted to examine longitudinal changes in major depressive disorder (MDD) and comorbid anxiety symptoms across assessment time points. The GLM-RM framework will be used to test the main effect of time, the main effect of treatment group (face-to-face vs. online EMDR), and the group × time interaction, which represents differential change over time between treatment modalities. Where significant effects are observed, planned post-hoc comparisons with Bonferroni correction [85] will be performed to examine changes in symptom severity between baseline (T01) and end of treatment (T04).

Finally, to account for repeated observations nested within individuals and to examine individual variability in symptom trajectories, hierarchical linear modeling (HLM) using maximum likelihood estimation will be employed, following the analytic guidelines described by Garson [86]. In these models, Level-1 will represent repeated symptom measurements over time, and Level-2 will represent individual participants. Time will be operationalized as the number of treatment sessions from baseline to follow-up and coded sequentially (e.g., 1, 2, 3, 4, 5…). Predictor variables will be entered as covariates and examined as fixed effects (representing average effects across participants) and, where appropriate, as random effects (representing individual variability in intercepts and slopes). Given the frequent co-occurrence of depressive and anxiety symptoms [87], reciprocal associations between depression and anxiety over time will be examined using HLM-based reciprocal association methodology [77, 80] and a 1–1–1 multilevel mediation modeling approach [88, 89].

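### Hypothesis (iii) attributes an uncontrolled before–after fall in depression scores to the therapy; with two EMDR arms, the main effect of time cannot show effectiveness.

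*Protocol article*

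**What the plan says.** Under Hypotheses of study, the third directional hypothesis reads: "The adapted EMDR therapy will bring about significant temporal reduction in the major depressive disorder symptoms across in-person and online modes". It serves the third objective, "To assess the clinical effectiveness of the adapted DeprEnd EMDR therapy protocol across in-person and online settings" (Objectives {7}). The primary outcome text under Outcomes {12} uses HAM-D-17 change from T01 to T03 for two purposes, clinical effectiveness and non-inferiority, so effectiveness stands as a claim of its own.

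Under Intervention description {11a}, "both study arms follow the same adapted protocol, differing only in mode of delivery". There is no untreated, waiting-list, usual-care or attention arm.

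Statistical methods {20a} plans a repeated-measures general linear model for phase three to "test the main effect of time, the main effect of treatment group (face-to-face vs. online EMDR), and the group × time interaction", followed where effects are significant by "planned post-hoc comparisons with Bonferroni correction". For phase two, the same section says the analyses are exploratory and not meant to establish definitive effectiveness. No such limit is placed on the phase three time effect.

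**The concern.** Randomisation protects the group effect and the group × time interaction. It does not protect the main effect of time, because every client receives the therapy and nobody shows what would have happened without it. The hypothesis is nonetheless worded causally and tied to effectiveness.

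The protocol itself supplies three rival explanations for a fall in scores:

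- **Regression to the mean.** Clients are selected on a high score, HAM-D-17 ≥ 20 (Who will take informed consent {26a}). Participant timeline {13} places enrolment and baseline assessment at the same time point, so the selecting score and the baseline appear to coincide.
- **Natural recovery.** Treatment runs 10–14 weekly sessions (Intervention description {11a}).
- **Co-medication.** Baseline antidepressants continue, and new ones may be prescribed in exceptional cases (Relevant concomitant care {11d}).

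Non-inferiority does not fill the gap, since two equally ineffective modes would also be non-inferior. Nor can local evidence stand in for a control: the background states that, to the authors' knowledge, "no published studies have clinically tested the DeprEnd EMDR therapy protocol in Pakistan". At stake is an effectiveness conclusion that the design cannot support.

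**Working it through.** **1. The plan's own figure.** Clients selection and sample size {14} gives n = (1.96 + 0.84)² × 2 × 8² / 5² = 7.84 × 128 / 25 = 40.14, stated as 40 per arm and 80 in total; 80 / 0.85 = 94.1, stated as 94. Both reproduce (40.14 rounded up would be 41). This sizing is for a 5-point difference between arms. The protocol gives no figure for the time effect in hypothesis (iii).

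**2. Inputs for the time effect.** SD of change 8, N = 80 (40 in one arm) and two-sided α = 0.05, all from that section. The calculation is a one-sample t-test of mean change against zero, a simple proxy for the repeated-measures time effect. The protocol does not say how many comparisons the Bonferroni correction covers. All six pairs of the four time points (4 × 3 / 2 = 6) is taken as an assumption, giving α = 0.05 / 6 = 0.0083.

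**3. Smallest significant mean fall** = t(1 − α/2, N − 1) × 8 / √N.

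- N = 80, α = 0.05: 1.990 × 0.894 = 1.78 points
- N = 80, α = 0.0083: 2.706 × 0.894 = 2.42 points
- n = 40, α = 0.05: 2.023 × 1.265 = 2.56 points
- n = 40, α = 0.0083: 2.780 × 1.265 = 3.52 points

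**4. Chance of a significant reduction when the therapy does nothing.** From the noncentral t with N − 1 degrees of freedom and noncentrality d / (8 / √N), where d is a purely non-specific mean fall. For N = 80:

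| Non-specific fall | α = 0.05 | Bonferroni, six pairs |
|---|---|---|
| 1 point | 20% | 6% |
| 2 points | 60% | 33% |
| 3 points | 91% | 74% |
| 4 points | 99% | 96% |

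For a 3-point fall at α = 0.05, the chance is 99% with SD 6 and 76% with SD 10.

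**5. How large might the non-specific fall be?** The protocol does not say. As an illustration only, regression to the mean after a cut-off of 20 is (1 − r) × (E[X | X ≥ 20] − μ), taking scores as normal with mean μ, SD s and retest correlation r. With s = 5–6 and r = 0.6–0.8 (all assumed):

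- μ = 15–18: 1.1 to 3.3 points
- μ = 20–22: 0.6 to 1.9 points

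Natural recovery and antidepressant effects would come on top, with no figure available for either.

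**6. Sample size is no remedy.** A larger N lowers the threshold in step 3 and leaves the non-specific fall where it is, so the bias does not shrink.

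**The case against.** The best defence is about scope. Trial design {8} presents phase three as a comparison of two modes in a non-inferiority framework, and Statistical methods {20a} puts that analysis first. Hypothesis (iii) alters neither the sample size, nor the randomisation, nor the non-inferiority decision. A two-mode trial without an untreated arm is a legitimate design. Treatment-naive clients are preferred, and new antidepressants are exceptional and documented, which limits confounding by medication. All of this stands, but none of it gives the time effect a control or removes the causal wording.

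Two stronger readings are tempting and should be resisted.

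- **That the test will confirm effectiveness almost whatever the therapy does.** The figures do not bear this out across the plausible range. At N = 80 without correction, a non-specific fall of 1.1 points reaches significance 23% of the time and one of 2 points 60%. The chance passes 90% only near 3 points, and Bonferroni lowers it further. The regression-to-the-mean inputs are assumptions. Source means of 15–18 may be low for clients already screened by a structured diagnostic interview for MDD.
- **That the comparator rationale is wrong.** Explanation for the choice of comparators {6b} says of in-person EMDR that "it represents the current evidence-based standard of care for the treatment of depressive disorder", and that the design can show whether online delivery preserves efficacy. It does not say that non-inferiority proves either mode works. Its statement is general and rests on a source not at hand. The background on limited local testing, which also mentions testing in Germany, does not strictly contradict it. That section needs no correction.

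It is also fair to say that a within-arm 95% CI carries the same numerical information as the two-sided 5% test. What the change corrects is what the result is said to mean.

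**Conclusion.** The point holds as one of inference. No contrast in the design separates the therapy from time, yet hypothesis (iii) says the therapy causes the fall, and the effectiveness objective and endpoint depend on it. The protocol accepts the principle for its single-group phase two. The phase three time effect is the same kind of inference with more clients and lacks the caveat.

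The size depends on an unknown. Given SD 8, N = 80 and the t-test proxy, a therapy with no effect would still produce a significant reduction with high probability if the non-specific fall is about 3 points or more, and much less often at 1–2 points. The underlying fault does not depend on that figure. Absolute efficacy of the adapted protocol is assumed in this trial, not tested. The randomised non-inferiority comparison in hypothesis (ii) is untouched.

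**What to change.** - Reword hypothesis (iii), and the effectiveness part of Objectives {7} and Outcomes {12}, as within-arm change in HAM-D-17 over time, reported with 95% CI and not attributed to the therapy.
- In Statistical methods {20a}, extend the phase two caveat to the phase three main effect of time.
- Confine causal conclusions to the randomised online versus in-person contrast (non-inferiority and group × time), stated as relative efficacy only.
- Optionally, add a sentence noting that absolute efficacy of the adapted protocol is assumed rather than tested.

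The cost is wording. Sample size, data collection and the planned models stay as they are. The sponsor gives up an effectiveness claim that only a control condition could support.
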